#### **4.2.7. Inclusion Criteria (Prodromal Subjects)**

- 4.2.7.1. Subjects must have at least one of the following characteristics:
  - Hyposmia:*
    - a) Male or female age 60 years or older
    - b) Confirmation from olfactory core that olfaction as determined by UPSIT is at or below the 10th percentile by age and gender
  - REM Behavior Disorder (RBD):*

- a) Male or female age 60 years or older
  - b) Confirmation from sleep core that subject's Polysomnography (PSG) meets criteria for RBD and/or clinical diagnosis of RBD by site investigator including existing PSG.
- 4.2.7.2. Confirmation from imaging core that screening dopamine transporter SPECT scan (or V-MAT-2 PET scan for sites where DaTSCAN™ is not available) is read as eligible (see below)
- About 80 subjects will have a range of DAT deficit similar to subjects with early PD (mild to moderate DAT deficit). About 20 subjects will be selected with no DAT deficit or minimal DAT deficit similar in age, gender, and risk profile to those with mild to moderate DAT deficit.
- 4.2.7.3. Ability to provide written informed consent in accordance with Good Clinical Practice (GCP), International Conference on Harmonization (ICH), and local regulations.
- 4.2.7.4. Willing and able to comply with scheduled visits, required study procedures and laboratory tests.
- 4.2.7.5. Women may not be pregnant, lactating or planning pregnancy during the course of the study.
- Includes a negative urine pregnancy test on day of screening scan prior to injection (DaTSCAN™).
  - Includes a negative serum pregnancy test prior to Screening scan injection (F-AV-133 only).
- 4.2.7.6. Women participating in VMAT-2 PET imaging must be of non-childbearing potential **or** be using a highly effective method of birth control 14 days prior to until at least 24 hours after injection of F-AV-133).
- Non-child bearing potential is defined as a female that must be either postmenopausal (no menses for at least 12 months prior to Screening) or surgically sterile (bilateral tubal ligation, bilateral oophorectomy or hysterectomy).

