## **14. Statistical Methods**

### **14.1 Statistical Design**

PPMI is a longitudinal, multi-center study to assess progression of clinical features and imaging and biomic biomarkers in Parkinson disease patients and healthy controls. PD, Prodromal (including the Prodromal and Unaffected Genetic Cohort) and control subjects will be evaluated longitudinally for at least 36 months.

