### 14.3 Secondary Objectives

- 14.3.1 Comparison between the rates of change in the mean of clinical, imaging and biomic outcomes in various subsets (including, but not limited to: early PD patients and vs. healthy subjects, PD vs. SWEDD, PD vs. Prodromal, PD with and without LRRK2, GBA or SNCA mutation, unaffected LRRK2, GBA or SNCA mutation carriers vs. healthy subjects) at study intervals ranging from 3 months to 156 months.
- 14.3.1. To determine the prevalence of measures of clinical, imaging and biomic outcomes in various subsets (including, but not limited to: early PD patients vs. healthy subjects PD vs. SWEDD, PD vs. Prodromal, PD with and without LRRK2, GBA or SNCA mutation, unaffected LRRK2, GBA or SNCA mutation carriers vs. healthy subjects) at study intervals ranging from baseline to 156 months.
- 14.3.2. To establish the predictive value of early clinical non-motor features, baseline imaging and biomic outcomes for future course of disease.
- 14.3.3. To examine the proportion of SWEDD subjects that have a change in their clinical management at 24 months (SWEDD Clinical Diagnosis and Management Questionnaire).
- 14.3.4. To examine the proportion of Prodromal subjects with one or more risk characteristics [hyposmia (<10th percentile by age and gender), RBD, or LRRK2, GBA or SNCA mutation, and baseline DaTSCAN binding showing minimal to moderate DAT deficit who phenoconvert within two years. To correlate the baseline DaTSCAN binding with risk of phenoconversion
- 14.3.5. To conduct exploratory analyses to examine whether the baseline DaTSCAN binding or progression of clinical, imaging, or biospecimen biomarkers will predict those subjects likely to phenoconvert.
- 14.3.6. Exploratory analysis of SWEDD subjects with substantial evidence of PD followed for longer than 2 years compared to PD subjects

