- 14.4.6. **Exploratory analysis of Prodromal subjects that phenoconvert.** The analysis will involve estimating the percentage of Prodromal subjects that

phenoconvert to PD within 2 years. The percentage and 95% confidence interval will be reported.

**14.4.7. Exploratory analyses of biomarkers for predicting phenoconversion among Prodromal Subjects.** This set of analyses will examine whether short-term changes in the progression endpoints are predictive of phenoconversion among Prodromal subjects. All progression endpoints will be considered. The examination will involve fitting a logistic regression model for phenoconversion, with each progression endpoint serving as a covariate.

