| 300               | 0.16                   | 17%                                 | 0.33                                          |
| 400               | 0.14                   | 14%                                 | 0.28                                          |
| 450               | 0.14                   | 15%                                 | 0.28                                          |
| 600               | 0.11                   | 13%                                 | 0.24                                          |

The planned sample size of approximately 80 SWEDD subjects is based on the estimated percentage of SWEDD subjects that will be observed over the recruitment period for the PPMI study. This is based on preliminary data from the study suggesting that about 20% of subjects screened with parkinsonian symptoms have no evidence for dopamine transporter deficit. The clinical and biomarker data from the SWEDD subjects will serve as a disease control population and will allow for a number of important exploratory assessments comparing the SWEDD subjects to the PPMI PD subjects and Healthy Controls.

The planned sample size of approximately 100 for the prodromal cohort is based primarily on prior exploratory studies. Nevertheless, based on preliminary data from studies combining olfactory loss, RBD, or LRRK2 mutation with DAT imaging deficit to define an at-risk population, we estimate 30% phenoconversion during the 24 month evaluation post DAT imaging. Under this assumption, the sample size will allow estimating the phenoconversion rate with a 95% confidence interval width of approximately  $\pm 10\%$ . It is further anticipated that the change in clinical, imaging, and biomarker data from the Prodromal cohort will allow for a number of important exploratory assessments comparing Prodromal subjects who convert to Prodromal subjects who do not convert. Finally, additional exploratory assessments will compare the Prodromal subjects to the PPMI PD subjects, Healthy Controls, and SWEDD subjects.

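### The single two-year phenoconversion percentage in 14.4.6 depends on the 80:20 enrolment quota and does not match the group named in 14.3.4 or the DAT-deficit populations behind the 30% in 14.5

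*Protocol*

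**What the plan says.** Protocol 14.4.6 describes the analysis in two sentences. It opens with "The analysis will involve estimating the percentage of Prodromal subjects that", and then gives the event, the time window and the output: "phenoconvert to PD within 2 years. The percentage and 95% confidence interval will be reported". It mentions neither DAT status nor strata.

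The composition of the cohort is set at eligibility. Section 4.2.7.2 states: "About 80 subjects will have a range of DAT deficit similar to subjects with early PD (mild to moderate DAT deficit"). It continues: "About 20 subjects will be selected with no DAT deficit or minimal DAT deficit similar in age, gender, and risk profile" to the first group. Section 4.1 repeats the split and adds that about 400 screening scans are expected in order to find the 100.

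The matching objective, 14.3.4, is narrower. It asks for the proportion with a risk characteristic and "baseline DaTSCAN binding showing minimal to moderate DAT deficit who phenoconvert within two years". The secondary outcome in 3.2(e) uses the same restriction.

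Section 14.5 says "The planned sample size of approximately 100 for the prodromal cohort is based primarily on prior exploratory studies". It then cites preliminary studies that combined olfactory loss, RBD or LRRK2 mutation with a DAT imaging deficit, and concludes "we estimate 30% phenoconversion during the 24 month evaluation post DAT imaging". From this it derives an interval of approximately ±10%.

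The word Prodromal also changes scope. Section 14.1 has "Prodromal (including the Prodromal and Unaffected Genetic Cohort) and control subjects will be evaluated longitudinally for at least 36 months", and objective 2.2.5 uses the same wide meaning. Section 4.1 limits the prodromal cohort to 100 subjects with RBD and/or hyposmia and moves the LRRK2 component to the Genetic Cohort. Section 14.5 likewise sizes the prodromal cohort at about 100.

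**The concern.** The share of subjects without a clear deficit is the sponsor's choice. A single percentage over both groups would change if the quota changed, even with the same risk in each group. It equals the risk in people with hyposmia or RBD only if their natural mix happens to be about 80:20, and the protocol does not give that mix.

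The sections also disagree on who is in the denominator. Section 14.3.4 requires at least a minimal deficit and 14.4.6 requires none. Subjects with minimal deficit are inside the target in 3.2(e) and 14.3.4, but 4.2.7.2 groups them with the no-deficit comparison subjects.

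The conversion percentage is a listed secondary outcome. If the observed figure falls below 30%, the reader could not tell whether risk in the deficit group was lower than expected or whether the 20 comparison subjects diluted it.

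**Working it through.** **Inputs from the protocol**
- Cohort of about 100: 4.1 and 14.5.
- About 80 with mild to moderate deficit and about 20 with none or minimal: 4.1 and 4.2.7.2.
- 30% conversion at 24 months, from DAT-deficit populations that included LRRK2 carriers: 14.5.
- Stated precision of approximately ±10%: 14.5.

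**Assumption.** The protocol gives no conversion rate for the no/minimal-deficit group. I call it p0 and let it run from 0 to 10%.

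**1. Reproducing the ±10%.** Half-width = 1.96 × √(p(1−p)/n), with p = 0.30.
- n = 100: 1.96 × √(0.21/100) = 0.090, or ±9.0 points. The exact (Clopper-Pearson) interval for 30/100 is 21.2 to 40.0%.
- n = 80: 1.96 × √(0.21/80) = 0.100, or ±10.0 points.
- n needed for ±10 points: 1.96² × 0.21/0.01 = 80.7, so 81.

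The stated precision is approximately right for either denominator.

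**2. What the pooled percentage should be expected to show.** Pooled = (80 × 0.30 + 20 × p0)/100.
- p0 = 0: 24/100 = 24%.
- p0 = 5%: 25/100 = 25%.
- p0 = 10%: 26/100 = 26%.

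The binomial half-width at 24 to 26% with n = 100 is ±8.4 to ±8.6 points, so ±10% is slightly conservative for the pooled cohort.

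**3. Dependence on the quota alone.** Stratum risks are held at 30% and p0 = 0 to 10%, and only the enrolled mix changes.

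| Mix (deficit : no/minimal) | Pooled percentage |
|---|---|
| 90:10 | 27 to 28% |
| 80:20 (planned) | 24 to 26% |
| 70:30 | 21 to 24% |
| 50:50 | 15 to 20% |

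**4. Denominators side by side.**

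| Section | Group implied | Approximate size |
|---|---|---|
| 14.4.6 | All Prodromal subjects | 100 |
| 3.2(e), 14.3.4 | Minimal to moderate deficit | Between 80 and 100; the number of the 20 with minimal deficit is not given |
| Source of the 30% in 14.5 | At-risk subjects with DAT deficit, LRRK2 carriers included | Closest to the 80 |
| 14.1, 2.2.5 wording | Prodromal cohort plus Unaffected Genetic Cohort | 100 + 300 |

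**5. Price of reporting the small stratum alone.** With 0 events in 20, the exact two-sided 95% upper limit is 1 − 0.025^(1/20) = 0.168, about 17%.

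**The case against.** The strongest reply is that 14.4.6 should be read with its objective. Section 14.3.4 already restricts the target by DAT deficit and plans to correlate baseline binding with conversion, and 14.3.5 examines binding as a predictor. The analysis is labelled exploratory, 14.4 leaves further detail to the PPMI Data Analysis Plan, and a 4 to 6 point dilution lies inside the planned interval. Most of this stands. DAT status is not ignored, and it would be too strong to say that the estimate has no definable target. But the two sections state different denominators, a correlation does not repair the headline percentage, and 14.4.5 shows that the protocol can split a result by transporter deficit when it wants to.

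Some stronger readings are tempting but are not supported:

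- *The ±10% describes only the deficit stratum.* Section 14.5 attaches it to about 100 subjects, and it fits there loosely. The 80 fit more closely, but that does not make it a figure for the 80.
- *The percentage will be taken over 400 people.* The wide use of Prodromal in 14.1 and 2.2.5 could suggest this. If the 300 unaffected genetic subjects converted at 0 to 5% (assumption), the pooled result would be about 6 to 10%. But 14.1 is a sentence about follow-up, 4.1 and 14.5 keep the cohorts apart, and 14.5 plans to compare them. The wording needs tidying; no section plans that percentage.
- *Withdrawals of 25% widen the interval to about ±12% or bias the estimate.* Section 14.5 gives 25% only for the PD and the PD/HC samples, and 14.4.6 does not fix how early withdrawals are counted. Neither a loss rate nor a direction of bias can be read from the protocol. A Kaplan-Meier estimate is an option for the Data Analysis Plan.
- *The risk among those scanned is a specific lower figure.* That requires the DAT split among the 400, which is not stated.

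**Conclusion.** The point holds, at moderate weight. The single percentage in 14.4.6 mixes two groups in a ratio set by selection and does not match the target in 3.2(e) and 14.3.4. The 30% in 14.5 comes from DAT-deficit populations but is applied to a cohort of which about a fifth is chosen for having no or minimal deficit. If 30% is right for the 80 and the 20 convert at 0 to 10%, the pooled expectation is about 24 to 26%, which is 4 to 6 points below the planning figure. Both conditions are assumptions. The 30% is itself not a clean figure for the present deficit stratum, because its sources included LRRK2 carriers who have since moved to the Genetic Cohort. The mismatch lies in the 30% and the target group, not in the stated precision.

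**What to change.** - **14.4.6:** report the 24-month percentage with its 95% confidence interval separately for the mild-to-moderate-deficit stratum (about 80) and the no/minimal-deficit stratum (about 20). Report the Unaffected Genetic Cohort separately as well, which also serves objective 2.2.3.
- **Definitions:** reconcile Prodromal (14.1 and 2.2.5 against 4.1 and 14.5) and minimal deficit (3.2(e) and 14.3.4 against 4.2.7.2), so that one analysis target runs through all sections. Either boundary for minimal can serve if it is used consistently.
- **14.5:** tie the 30% and the ±10% to the roughly 80 subjects with deficit (±10.0 points), and note that the source studies included LRRK2 carriers.

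No change to data collection is needed. The cost is an amendment to wording, including that of a secondary outcome if the boundary for minimal is moved in 3.2(e), and a wide interval for the 20-subject stratum (upper limit about 17% even with no events). That width is a fair picture of what 20 subjects can show.

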#### **5.3.4. Baseline Visit (Day 0):**

The activities at the baseline visit will be completed within 45 days of completing the Screening visit. The Baseline visit will include the following activities and will take about 6 hours to complete. All assessments and activities listed below must be completed prior to enrollment of the subject into the study.

- Review of continuing ability to consent/Advance Directive
- Review willingness to share contact information with FOUND or, if enrolled in FOUND, review individual status report
- Height and weight
- Vital signs (blood pressure, heart rate and temperature)
- Blood draws for research samples (including blood draw for PBMCs)

- Urine collection for research samples
- Olfactory testing using the University of Pennsylvania Smell Identification Test (UPSIT)
- Clinical diagnosis assessment (SWEDD and Prodromal subjects only)
- Review of family history of PD (Genetic Cohort subjects only)
- Provide Family History substudy packet to subject (may be completed at a later visit for subjects enrolled prior to Amendment 8 approval); Record PPMI subject ID on Family Packet distribution sheet and fax to Indiana University (Genetic Cohort subjects only)
- PASE Exercise Questionnaire (Prodromal and Genetic Cohort subjects only)
- Epworth Sleepiness Scale
- REM Sleep Behavior Disorder Questionnaire
- Geriatric Depression Scale (GDS-15) (not applicable for Prodromal Subjects)
- State-Trait Anxiety Inventory (not applicable for Prodromal Subjects)
- Questionnaire for Impulsive-Compulsive Disorders
- Scales for Outcomes in Parkinson's Disease (SCOPA-AUT)
- Letter Number Sequencing
- Hopkins Verbal Learning Test – Revised (Form 1)
- Symbol Digit Modalities Test (Form 1)
- Benton Judgment of Line Orientation (Odd items)
- Semantic Fluency
- Cognitive Categorization Assessment
- MDS-UPDRS Parts I-III (Part IV also conducted at each visit for subjects who have started PD medication)
- Hoehn and Yahr
- Modified Schwab & England (PD, Prodromal, SWEDD, and Genetic Cohort subjects only)
- MDS-UPDRS Part III and Hoehn & Yahr will be repeated one hour following dosing in clinic for Genetic Cohort subjects (PD and Unaffected) who have started levodopa or dopamine agonist
- Brain magnetic resonance imaging (MRI), (MRI will include DTI and resting state sequences at selected sites only)
- Lumbar puncture for collection of cerebral spinal fluid (CSF)

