- 14.4.3. **Examination of whether short-term change in progression endpoints is predictive of change in long-term endpoints.** The third set of analyses will examine whether short-term changes in the progression endpoints are predictive of changes in long-term endpoints in the MDS-UPDRS score. This analysis will examine a subset of the progression endpoints. Only progression endpoints that show differences between subsets will be considered (since for example, a marker that doesn't distinguish PD patients from healthy subjects would not be thought to be a biomarker for long-term outcome in PD patients). All progression endpoints that meet these criteria will be modeled using a process similar to that described above. The primary focus will be on the long-term change in the UPDRS score. However, additional long-term endpoints may be considered as well. Because this modeling process involves longer term endpoints, which would be much harder to replicate, a ten-fold cross validation procedure will be used to test the predictive validity of each model. If successful, the final model will provide a subset of one or more short-term progression endpoints that are predictive of the change in one or more of the long-term endpoints. This would suggest that these short-term progression endpoints are valid biomarkers for future studies of interventions in PD patient populations.
- 14.4.4. **Examination of PD Subsets.** Each of the first three sets of analyses will be repeated comparing subsets of PD subjects, rather than PD subjects vs. healthy subjects. If successful, the final model from these subset comparisons will determine whether some of the short-term progression endpoints are more predictive of long-term change in the MDS-UPDRS score for some subsets of PD subjects and less predictive for other subsets of PD subjects.
- 14.4.5. **Calculation of the proportion of SWEDD subjects that have a change in diagnosis over the 24-month evaluation period.** The analysis will involve identifying all SWEDD subjects that have a change in diagnosis from PD to another diagnosis. The percentage and 95% confidence interval will be reported. The other possible diagnoses will be further divided into 2 categories: 1) Other parkinsonian syndrome with a dopamine transporter deficit; 2) Other condition without a dopamine transporter deficit. The same information will be reported as well by these two categories.

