The table below provides generic information about the detectable effect sizes for three types of statistical analysis that may be performed on the PPMI data. For each analysis the two-sided alpha level is set to 0.05 and the beta level to 0.80. The first column gives the total sample size assumed to be available for the analysis, in the first two rows either 400 (total PD sample) or 300 (PD sample after allowance for 25% withdrawals). The third and fourth rows of the table correspond to the total sample size of 600 (400 PD, 200 HC) when, respectively 75% and 100% of the subjects are available for analysis. The second column gives the detectable correlation coefficient between two continuous measures (e.g., change in striatal  $\beta$ -CIT uptake vs. change in total MDS-UPDRS). The third column gives the detectable difference in prevalence rates of some characteristic (e.g. presence of dopaminergic side effects) between two “halves” of the sample (e.g. the younger patients vs. the older patients, with age dichotomized at the median for the entire group). For the first two rows the third column gives the detectable “effect size”, expressed as ratio of difference in means to standard deviation, for comparing two “halves” of the sample (e.g. younger vs. older patients as above) in relation to a continuous measure (e.g. change in total MDS-UPDRS). For the third and fourth row the comparisons are between PD patients and HC. The table suggests that the PPMI trial is adequately powered to detect effects that would generally be of clinical interest. While possible that smaller effects than those listed in the table might also be of clinical interest, it was determined that the added power for these comparisons did not offset any additional costs and logistical issues that would accompany a larger study in this population. Rather, the proposed study should prove to be effective for screening a large number of variables and identifying those that show the most promise for further exploration in follow-up studies.

| Total sample size | Detectable Correlation | Detectable Difference in Prevalence | Detectable Difference in Means (Standardized) |
|--------------------------|-------------------------------|--------------------------------------------|------------------------------------------------------|

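### Section 14.4.6 plans a simple percentage for two-year phenoconversion, which cannot account for Prodromal subjects who withdraw before two years, and the protocol does not settle when the two years start

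*Protocol*

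**What the plan says.** Section 14.4.6 describes the analysis in two sentences. Its target is the share of the Prodromal cohort who "phenoconvert to PD within 2 years. The percentage and 95% confidence interval will be reported". Section 14.3.4 calls the same quantity a proportion, and section 14.4.7 models conversion by logistic regression, again as a yes/no outcome. The two-year figure is secondary outcome 3.2(e), and objective 2.2.3 asks for the probability of phenoconversion.

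Section 14.5 gives the planning basis: "The planned sample size of approximately 100 for the prodromal cohort" and "we estimate 30% phenoconversion during the 24 month evaluation post DAT imaging". On that basis it says that "the sample size will allow estimating the phenoconversion rate with a 95% confidence interval width of approximately"; the figure given is ±10%. No allowance for withdrawal is made there. The only withdrawal figure in the protocol is for another cohort: "300 (PD sample after allowance for 25% withdrawals".

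On timing, sections 14.5 and 1.1 (under the prodromal biomarker landscape) count the two years from DAT imaging. Section 5.2 places that scan in the Screening visit, and section 5.3.4 adds "The activities at the baseline visit will be completed within 45 days of completing the Screening visit". The Prodromal Schedule of Activities counts Month 24 from Baseline with a ±30-day window.

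**The concern.** Conversion is observed only while someone is assessing the subject. The protocol foresees withdrawal: it has a premature withdrawal visit (5.3.23), and section 9.1 withdraws subjects who can no longer consent and have no advance directive. A subject who leaves unconverted at Month 9 is neither a two-year non-converter nor absent from the risk set for those nine months, but a simple percentage must treat that subject as one or the other.

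The result is a named secondary outcome, and readers designing prodromal trials would use it. The analyst's choice of denominator would move the estimate in a known direction, and an ordinary binomial interval would not show it. A second, smaller ambiguity is whether the two years run from the scan or from Baseline, and whether a diagnosis made a few days late at the Month 24 visit counts.

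**Working it through.** **The plan's own figure.** With p = 0.30 and n = 100, the half-width is 1.96 × √(0.30 × 0.70 / 100) = 0.090, or ±9.0 points. The exact interval is 21.2% to 40.0% (−8.8/+10.0). The stated ±10% therefore reproduces as a binomial interval on about 100 subjects, all with known two-year status.

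**Effect of withdrawal.** Inputs: a two-year risk of 30% (14.5), and a loss d within two years, which is assumed because the protocol gives none for this cohort. Hazards are assumed constant and independent.

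- Conversion hazard: λ = −ln(0.70)/2 = 0.1783 per year.
- Withdrawal hazard: μ = −ln(1 − d)/2.
- Converters observed, as a share of all enrolled: C = λ/(λ+μ) × [1 − 0.70(1 − d)].
- Followed to two years unconverted: S = 0.70(1 − d).
- All enrolled in the denominator: C. Withdrawn non-converters dropped: C/(C + S).

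For d = 25%: μ = 0.1438, S = 0.525 and C = 0.1783/0.3222 × 0.475 = 0.263. Per 100 enrolled, that is 26.3 observed converters, 52.5 followed unconverted and 21.2 lost. The two percentages are 26.3/100 = 26.3% and 26.3/78.8 = 33.4%.

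| Loss within two years | All in denominator (relative bias) | Withdrawn non-converters dropped (relative bias) |
|---|---|---|
| 5% | 29.3% (−2.4%) | 30.6% (+1.9%) |
| 10% | 28.6% (−4.8%) | 31.2% (+4.0%) |
| 15% | 27.8% (−7.3%) | 31.9% (+6.2%) |
| 20% | 27.1% (−9.8%) | 32.6% (+8.6%) |
| 25% | 26.3% (−12.4%) | 33.4% (+11.2%) |

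Under the same assumptions, a Kaplan-Meier estimate targets 30% at every level of loss. The two handlings differ by about 4 points at 15% loss and about 7 points at 25%. The relative bias passes 10% only above about 20.4% loss (all in denominator) or 22.7% (dropped).

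The 25% PD allowance has no stated time horizon. Spread over 3, 5 or 10 years, it implies two-year losses of 17.5%, 10.9% or 5.6%. The all-in-denominator bias is then −8.5%, −5.2% or −2.7%.

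**Time origin.** From Baseline, the ±30-day window is symmetric, so half of Month 24 visits fall after two years. For a clock from imaging, assume the scan is uniform over 0 to 45 days before Baseline and the visit uniform over ±30 days. The chance that the visit is not late is (30 × 30/2)/(60 × 45) = 1/6, so 83% fall after two years, by 22.5 days on average. Counting every conversion found at the in-window Month 24 visit gives no bias from Baseline and about +2.5% of the rate from imaging.

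**The case against.** The strongest objection is that 14.4 leaves further detail to a Data Analysis Plan that is not shown, and that denominators, censoring and visit windows normally belong there. The analysis is also labelled exploratory. That stands for the missing detail. It does not remove the point, because the protocol itself names the estimator: a percentage in 14.4.6, a proportion in 14.3.4, logistic regression in 14.4.7 and binomial precision in 14.5.

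Subjects who withdraw are also not wholly lost. The premature withdrawal visit includes a diagnosis assessment if the subject agrees, and FOUND (9.2) follows consenting subjects after withdrawal. This stands, and it makes the tabulated biases upper figures for a given loss.

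Three stronger readings are tempting, and the documents do not support them:

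- **That the plan keeps unobserved subjects in the denominator, so the rate is biased low by more than 10%.** The text names no denominator, and dropping these subjects fits it equally well with the opposite sign. The 25% is for PD subjects and has no horizon. Even at 25% loss the shift is 3.7 points, inside the planned ±9 to ±10.
- **That Month 24 visits mostly fall too late, so conversions are missed.** This holds only for a clock from imaging. A strict cut on visit date, with conversions found only at Months 18 and 24, would give −11.7% (Baseline) or −15.8% (imaging), but no section states such a cut. It also ignores capture between visits: calls at Months 15 and 21 that check for PD medication (5.3.21), 24-hour reporting of a changed diagnosis (section 11, Reportable Events) and the phenoconversion visit (5.3.27). If a Month 21 contact also finds conversions, the strict cut gives about −6% to −7%.
- **That 14.4.5 needs the same repair.** Section 4.1 normally makes the Month 24 questionnaire the final SWEDD diagnosis. That is a status at one visit, so a first-event analysis would answer a different question.

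**Conclusion.** The point holds as a modest defect of method. The simple percentage in 14.4.6 cannot handle withdrawal before two years. At 15 to 25% loss within two years, with a true 30% risk and constant hazards independent of each other, the bias is about 6 to 12% of the rate (roughly 2 to 4 points). It is downward if all subjects stay in the denominator and upward if withdrawn non-converters are dropped. It is smaller if loss is lower or if status is recovered after withdrawal. The loss figures are assumptions, because the protocol gives none for the Prodromal cohort. If withdrawal is related to conversion, the sizes would differ and a Kaplan-Meier estimate would not be free of bias either.

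The inconsistent time origin is real but minor: about 2.5% of the rate if in-window Month 24 diagnoses count. It needs one sentence to settle.

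**What to change.** Change 14.4.6 only:

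- Replace the simple percentage with the cumulative incidence of phenoconversion at 24 months, by Kaplan-Meier or by an interval-censored estimate (diagnosis is largely visit-based), with that method's own 95% confidence interval.
- Censor subjects without conversion at their last diagnosis assessment, including the one at the premature withdrawal visit.
- If deaths or other neurodegenerative diagnoses occur, treat them as competing events.
- Name one time origin, imaging or Baseline, and use it in 14.4.6 and 14.5 alike.
- State that a conversion found at the Month 24 visit within its ±30-day window counts as within two years.

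Leave 14.4.5 as a Month 24 status percentage. The cost is a few sentences and a standard survival procedure. No new data are needed, and the interval becomes slightly wider.
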